### Quality Control

The project leader will be responsible for the design, coordination, and quality control of the entire study. All researchers will undergo uniform training before the data collection period. Before data collection, patients are required to maintain a healthy lifestyle, such as avoiding staying up late and abstaining from alcohol, to prevent the influence of unstable factors. During the study, all data will be statistically analyzed by trained independent assessors. We will collect outcome data from all participants, regardless of whether they complete the study. The Data and Safety Monitoring Board will consist of an internal medicine physician, a Tai Chi instructor, a medical statistician, an ethicist, and a radiologist, and will conduct assessments throughout the study.

To ensure that the patients in the Tai Chi group can practice correctly at home, we will provide them with a video of Tai Chi practice methods recorded by a national Tai Chi champion, along with a booklet containing specific practice details. The Tai Chi group will also receive a practice record that will be filled out after each practice session.

### Data Collection and Management

Data entry and database creation will be handled by 2 data managers who are not part of the research team and are unaware of the group assignments. Everyone participating in the trial will have access to the full data set. All original data will be retained for clinical data analysis and safety evaluation. All research-related original data will be stored at Shanghai University of Traditional Chinese Medicine.

### Informed Consent

Before the trial begins, participants will be informed about the research process, their responsibilities, and the physical examinations and precautions involved. Most importantly, they will be informed that their participation is entirely voluntary and that they can refuse or withdraw at any time without affecting their medical care or other benefits. If a participant withdraws, the collected data will not be deleted and will be included in the final analysis. A written informed consent form will be obtained from each participant before starting any treatment related to the study. The research assistants will be responsible for obtaining informed consent from all participants.

### Statistical Analysis

All statistical analyses and processing will be independently performed by a researcher who did not participate in the treatment or scale assessments during the process. The Statistical Package for the Social Sciences version 20.0 (IBM Corporation) will be used for statistical analysis. Quantitative data with a normal distribution will be described as mean (SD). For quantitative data with a nonnormal distribution and outcome indicators, the rank-sum test will be used. A *P* value of <.05 indicates a statistically significant difference.

For the neuropsychological test outcome indicators, ANT, and N-Back test behavioral metrics, a 2 (group: Tai Chi group, education group) × 2 (time: pretest, posttest) repeated measures ANOVA will be used. For cases not meeting the sphericity test, the Greenhouse-Geisser method will be applied to correct the statistical data (degrees of freedom and *P* value), and Bonferroni correction will be applied for post hoc comparisons. All statistical inferences will be 2-tailed, with the level of significance set at α=.05. A *P* value of <.05 indicates statistically significant differences.

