**Methods:**

We will conduct a randomized, analyst-blinded, parallel-controlled trial with a 12-week intervention period and a 4-week follow-up. Enrolled patients will be randomly assigned to either the Tai Chi group (30 patients) or the health education group (30 patients). The Tai Chi group will receive the 24-style simplified Tai Chi intervention, while the control group will receive a health education intervention. Following the 12-week intervention, a 4-week follow-up will be conducted. The Tai Chi group will train 3 times per week, consisting of 2 in-person sessions at the Physical Education Center of Shanghai University of Traditional Chinese Medicine and 1 self-directed session guided online by an instructor. The primary outcome measure is the 20-item Multi-Dimensional Fatigue Inventory (MFI-20). The secondary outcome measures include the Montreal Cognitive Assessment (MoCA), Pittsburgh Sleep Quality Index (PSQI), Attention Network Test (ANT), working memory performance (N-Back task), and magnetic resonance imaging.

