### Outcome Measure Assessment

The outcome measures assessed include mental and physical fatigue, overall cognitive condition, attention, working memory, sleep quality, and resting-state MRI scans. Primary and secondary outcomes, along with related self-assessment scale measurements such as the MFI-20, Montreal Cognitive Assessment (MoCA), Attention Network Test (ANT), and Working Memory Test (N-Back), will be assessed at baseline (week 1), at the end of the intervention (week 13), and at follow-up (week 18). Table 1 presents the detailed outcome assessment time points.

**Table 1 table1:** Outline and timelines of the assessments.

Time points	Baseline (week 1)	Intervention period (weeks 2-13)	Postintervention (week 14)	Follow-up (week 18)
Inclusion criteria	✓	N/A^a^	N/A	N/A
Exclusion criteria	✓	N/A	N/A	N/A
Informed consent	✓	N/A	N/A	N/A
Randomization and allocation	✓	N/A	N/A	N/A
Intervention	N/A	✓	✓	N/A
20-item Multi-Dimensional Fatigue Inventory	✓	N/A	✓	✓
Montreal Cognitive Assessment	✓	N/A	✓	✓
Attention Network Test	✓	N/A	✓	✓
Working Memory Test (N-Back)	✓	N/A	✓	✓
Pittsburgh Sleep Quality Index	✓	N/A	✓	✓
Amplitude of low-frequency fluctuation	✓	N/A	✓	N/A
Functional connectivity	✓	N/A	✓	N/A
Adverse events	N/A	✓	✓	✓

^a^N/A: not applicable.

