### Demographic and Clinical Characteristics of the Participants

The researchers will collect data on the demographic characteristics of the participants (such as age, sex, education level, marital status, living arrangements, occupation, and socioeconomic status), as well as their medical and medication history using a self-designed questionnaire. Baseline assessments will be completed before randomization.

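### On any reading of the Statistical Analysis section, baseline MFI-20 is not a covariate in the primary comparison, so precision that ANCOVA would recover is given up

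*Protocol article*

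**What the plan says.** The Abstract fixes the primary outcome: "The primary outcome measure is the 20-item Multi-Dimensional Fatigue Inventory (MFI-20").

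The Statistical Analysis section has two inferential rules for non-imaging data. The first reads "For quantitative data with a nonnormal distribution and outcome indicators, the rank-sum test will be used". The second is a group-by-time repeated measures ANOVA, with scope "For the neuropsychological test outcome indicators, ANT, and N-Back test behavioral metrics". MFI-20 is not named under either rule. Outcome Measure Assessment groups it with the self-report scales ("along with related self-assessment scale measurements such as the MFI-20"), and the Discussion gives ANT and N-Back as its examples of neuropsychological paradigms. The first rule is therefore the more natural home for MFI-20.

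Baseline fatigue is available for everyone. The scales "will be assessed at baseline (week 1), at the end of the intervention (week 13), and at follow-up (week 18"), and under Demographic and Clinical Characteristics, "Baseline assessments will be completed before randomization". The section on neuroimaging results deals with ALFF, connectivity, correlations and imputation, not with the MFI-20 group comparison. No section mentions a covariate, ANCOVA or a mixed model for MFI-20.

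**The concern.** A fatigue score taken before randomization is usually the strongest available predictor of the same score 12 weeks later. Using it as a covariate removes the part of the outcome variance that it explains. A rank-sum test takes no covariate, and the group-by-time interaction in a 2 × 2 ANOVA amounts to a t test on change scores, which over-subtracts baseline whenever the correlation is below 1. So each analysis that the text could mean leaves precision unused.

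The trial has only 60 participants and is meant to inform a larger one. For that, the useful product is an estimated difference on the MFI-20 scale with as narrow a confidence interval as the data allow. The test that most plausibly applies to MFI-20 also differs from the t test used for the sample size.

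**Working it through.** **Inputs from the document.** Sample Size Calculation: means 4.80 (SD 2.11) and 7.13 (SD 3.29), d=0.843, two-sided α=0.05, power 0.80, 24 per group, 20% dropout, 30 per group. I use d only as the plan's own standardised effect.

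**Assumed input.** The correlation r between baseline and postintervention MFI-20 is not given; the range taken is 0.3 to 0.7.

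**1. The plan's figure reproduces.** Pooled SD = √((2.11² + 3.29²)/2) = 2.764. d = (7.13 − 4.80)/2.764 = 0.843. The noncentral-t sample size is 23.09, rounded up to 24 per group (power 0.816 at 24). Then 24/(1 − 0.20) = 30.

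**2. Variance of the group difference, relative to a comparison of post-score means.** With equal SDs at both visits, post scores give 1, change scores 2(1 − r), and ANCOVA 1 − r². ANCOVA relative to change scores is therefore (1 − r²)/(2(1 − r)) = (1 + r)/2.

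| r | ANCOVA / post | Change / post | ANCOVA / change |
|---|---|---|---|
| 0.3 | 0.91 | 1.40 | 0.65 |
| 0.5 | 0.75 | 1.00 | 0.75 |
| 0.7 | 0.51 | 0.60 | 0.85 |

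ANCOVA variance is thus 9% to 49% below the post-score comparison and 15% to 35% below change scores. For normal data the rank-sum test has efficiency 3/π = 0.955 relative to the t test. Its large-sample variance is then 1/(0.955 × (1 − r²)) times that of ANCOVA, or 1.15, 1.40 and 2.05 at r = 0.3, 0.5 and 0.7.

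**3. Sample size needed per arm at d=0.843 and 80% power.** Unadjusted t test 24; rank-sum 23.09/0.955 = 24.18, so 25; ANCOVA 22, 18 and 13 at r = 0.3, 0.5 and 0.7.

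**4. Simulated power** (normal data, 3,000 runs per setting, d=0.843, 24 completers per arm):

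| r | Rank-sum, post | Rank-sum, change | t test on change (ANOVA interaction) | ANCOVA |
|---|---|---|---|---|
| 0.3 | 0.782 | 0.653 | 0.680 | 0.836 |
| 0.5 | 0.786 | 0.798 | 0.821 | 0.898 |
| 0.7 | 0.797 | 0.950 | 0.962 | 0.981 |

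The true post-score rank-sum power does not depend on r, so the spread in that column is simulation error. With all 30 per arm, rank-sum on post scores gives about 0.88–0.89 and ANCOVA 0.92, 0.96 and 0.99. If the true effect were smaller, say d=0.5 (assumed) with 30 per arm, rank-sum on post scores gives about 0.45–0.46 and ANCOVA 0.49, 0.60 and 0.75.

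ANCOVA is ahead of every alternative in each row. How far ahead depends on r and on which alternative is meant.

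**The case against.** Several points on the other side stand.

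- **The text is ambiguous.** A reader might infer that the plan definitely fixes a rank-sum test on unadjusted post scores. It does not. The sentence can be read as applying only where outcome data are nonnormal. Taken literally for all outcomes, it would collide with the next paragraph, which sends some outcome measures to ANOVA. That paragraph also lists neuropsychological indicators separately from ANT and N-Back, so it covers at least one further scale and does not expressly exclude MFI-20. Nor does the text say that baseline is ignored: ranking change scores would use it, though not as a covariate.
- **Validity is not in question.** A reader might infer bias from chance baseline imbalance. Under 1:1 randomization the rank-sum test keeps its type I error, chance imbalance included.
- **The pilot will not lack an SD.** The section plans mean (SD) for normally distributed data, so the stronger claim that no SD will be available fails.
- **The trial is not underpowered on its own assumption.** Post-score rank-sum power stays near 0.80 with 24 completers. The mismatch with the planning t test moves the requirement only from 24 to about 25, inside the 30 recruited.
- **Covariates are often left to an analysis plan,** which may exist here. However, the article does name its tests, and none of those that could apply to MFI-20 adjusts for baseline. The point is therefore about a stated choice of method and not only about missing detail.

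**Conclusion.** The point holds as a loss of efficiency. On the most natural reading MFI-20 goes to a rank-sum test, and on all three possible readings its prerandomization value is not a covariate. At d=0.843 with 24 per arm, the gain from ANCOVA over post-score rank-sum runs from about 0.05 in power at r=0.3 to about 0.18 at r=0.7. Against change-score rank-sum it runs from about 0.18 at r=0.3 to 0.03 at r=0.7.

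These sizes rest on an assumed correlation, roughly normal scores and equal SDs. With r near zero, only the roughly 5% rank-sum efficiency loss would remain against post scores. The gain matters more if the true effect is below 0.843.

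The documents do not support calling the primary comparison invalid or the trial underpowered at its planning effect. This should be fixed because it costs nothing; it is not a defect that blocks the trial.

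**What to change.** In Statistical Analysis, state that the MFI-20 total at the postintervention assessment is compared between groups by ANCOVA, or an equivalent mixed model, with baseline MFI-20 as covariate. Report the adjusted mean difference with its 95% CI, and keep the rank-sum test as a sensitivity analysis, saying which scores it ranks. Naming MFI-20 explicitly also removes the ambiguity over which rule governs it.

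The cost is wording only. Baseline MFI-20 is already scheduled, the Results section says that statistical analysis has not been performed, and Ethical Considerations gives the route for a protocol change through the ethics committee. The change should be made and dated before the analyst works with outcome data by group.

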### Follow-Up Period

Follow-up will be conducted 4 weeks after the end of the trial, during which all participants will return to their original lifestyle. However, participants will be required to log their daily exercise or study activities. They will use WeChat to take weekly photos, providing researchers with evidence of their daily exercises or studies. At the end of the follow-up period, participants’ fatigue, attention, and working memory will be reevaluated. The follow-up assessment aims to assess the long-term effects of Tai Chi on patients with CFS. Additionally, at the end of the follow-up assessment, participants will receive a special Tai Chi souvenir to encourage their enthusiasm for the follow-up.

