#### N-Back Test

This study uses the N-Back task paradigm to assess working memory, one of the classic experimental approaches for evaluating this cognitive function. The task is implemented using E-Prime 3.0 software and is performed on a computer with a keyboard. It presents stimuli and records participants’ reaction times and accuracy rates across all trials. During the test, participants are required to sit in front of the computer screen, maintaining a horizontal distance of 60 cm. The index fingers of the participant’s left and right hands should lightly touch the F and J keys on the keyboard, ready to respond by pressing a key when a letter appears. The N-Back paradigm includes 3 levels of memory load (0=back, 1=back, and 2=back tasks), with stimuli consisting of the letters A, B, C, D, E, and F against a black screen background with white letters. At the start of the experiment, a “+” is first displayed for 500 ms, followed by the random presentation of English letters. Each stimulus is presented for 500 ms, with an interstimulus interval of 2000 ms (blank screen). If no response is made within 2000 ms, the next stimulus is automatically presented. After each block, a prompt message saying, “Please rest for a moment; press the space bar to continue” appears. In the 0=back task, participants are instructed to compare the current letter with “X” and press the F key if they are the same or the J key if they are different. In the 1=back task, starting from the second letter, participants are instructed to determine whether the current letter is the same as the previous letter, pressing the F key if they are the same or the J key if they are different. In the 2=back task, starting from the third letter, participants are instructed to determine whether the current letter is the same as the letter 2 positions back, pressing the F key if they are the same or the J key if they are different. Participants are required to respond both quickly and accurately. The task includes 60 practice trials, followed by the formal experiment, which consists of 9 blocks, each with 30 trials (15 targets and 15 nontargets). Each memory load level includes 3 blocks, with the 0=back, 1=back, and 2=back tasks completed in sequence. Each task type involves a total of 90 stimuli (30 × 3), with a target-to-nontarget ratio of 1:1, presented in a pseudorandom order. The behavioral metrics include reaction time and accuracy rate.

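### The ANOVA stated for the neuropsychological, ANT and N-Back outcomes has only two time levels, so it cannot use the week-18 visit, and its sphericity rule has no effect

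*Protocol article*

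**What the plan says.** The Statistical Analysis section of the protocol article sets the scope of its model with "For the neuropsychological test outcome indicators, ANT, and N-Back test behavioral metrics" and then crosses group (Tai Chi, education) with time: "2 (time: pretest, posttest) repeated measures ANOVA will be used". It adds two rules: "For cases not meeting the sphericity test, the Greenhouse-Geisser method will be applied to correct the statistical data", and "Bonferroni correction will be applied for post hoc comparisons". The only other general test it names is in this sentence: "For quantitative data with a nonnormal distribution and outcome indicators, the rank-sum test will be used". That sentence gives no time point.

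The schedule has three occasions. Outcome Measure Assessment and Table 1 place MFI-20, MoCA, ANT, N-Back and PSQI at baseline, after the intervention and at week 18. The Follow-Up Period section lists fatigue, attention and working memory as measured again at the end of follow-up, and gives the reason: "The follow-up assessment aims to assess the long-term effects of Tai Chi on patients with CFS".

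**The concern.** The article does not leave the model open. It names both factors and every level of each, and the levels of time do not match the visits at which these outcomes are measured. If the text is followed, the visit collected to show whether an effect lasts adds nothing to the analysis of attention, working memory and cognition. If it is not followed, the article gives no rule for what replaces it, and a method for judging persistence might be picked once the data are in view.

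The sphericity sentence shows the same mismatch from inside the paragraph. It is a rule for a within-person factor with three or more levels, and the stated model has none. A reader cannot tell whether three visits were intended and mis-stated as two, or whether the sentence was carried over from another design.

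**Working it through.** **1. Schedule against model**

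- Visits for MoCA, ANT and N-Back: baseline, postintervention, week 18, so 3 (Outcome Measure Assessment, Table 1). The text puts the middle visit at week 13 and the table at week 14, which does not affect the count.
- Levels of time in the stated model: pretest and posttest, so 2 (Statistical Analysis).
- Visits left out: 3 - 2 = 1, the one to which the Follow-Up Period section gives its own aim.
- Other stated analyses: the rank-sum sentence names no visit. The imaging tests are before-and-after comparisons, which fits Table 1 because imaging is not repeated at week 18. Neither names the week-18 data.

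**2. Sphericity with two levels**

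The Greenhouse-Geisser epsilon for k levels is tr(A)² / [(k - 1) tr(A²)], where A is the double-centred k x k covariance matrix. For k = 2, let the variances be a and b and the covariance c.

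- A = [(a + b - 2c)/4] times the matrix with rows (1, -1) and (-1, 1).
- tr(A) = (a + b - 2c)/2, so tr(A)² = (a + b - 2c)²/4.
- tr(A²) = 4 x [(a + b - 2c)/4]² = (a + b - 2c)²/4.
- epsilon = tr(A)² / [1 x tr(A²)] = 1, whatever a, b and c are.

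Mauchly's test has k(k - 1)/2 - 1 degrees of freedom, which is 2 x 1/2 - 1 = 0 for k = 2. There is nothing to test and nothing to correct.

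**3. The same quantities with week 18 added (N = 60, two groups)**

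| | k = 2 (stated) | k = 3 (week 18 included) |
|---|---|---|
| Group-by-time df: (k - 1) and (60 - 2)(k - 1) | 1 and 58 | 2 and 116 |
| Mauchly df | 0 | 2 |
| Lower bound of epsilon: 1/(k - 1) | 1 | 0.5 |
| Epsilon over 20,000 random covariance matrices | 1.000 to 1.000 | 0.502 to 1.000 |
| Pairwise time contrasts: k(k - 1)/2 | 1 | 3 |

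The correction can change a result only in the right-hand column.

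**4. Sample size**

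The plan's own figure reproduces. The pooled SD is √[(2.11² + 3.29²)/2] = 2.764, and d = (7.13 - 4.80)/2.764 = 0.843. The two-sided t test at 5% with 80% power needs 23.09, so 24 per group, and 24/(1 - 0.20) = 30. That calculation rests on a two-group t test, so adding week 18 to the analysis model does not alter it.

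**The case against.** The strongest reply is that this is a condensed article, that a fuller plan may exist, and that silence about week 18 proves nothing. That holds for outcomes on which the article is silent. It does not hold where the article lists the levels of time: a fuller plan that used week 18 would contradict this text, so the text needs correcting either way.

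Several stronger conclusions might be drawn, and the document does not support them.

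- **That week 18 is never analysed.** The rank-sum sentence neither includes nor excludes it, and an unseen plan may cover it. What can be said is that no stated analysis names it. For the same reason, one cannot say that any week-18 analysis would be chosen after seeing the data: the Results section reports that no analysis had yet been run.
- **That the two-level limit covers all five instruments.** The model is stated for the neuropsychological, ANT and N-Back measures. MFI-20, the primary outcome, and PSQI are not named in it. For those two the article names no longitudinal model, which is a different and weaker observation.
- **That the Bonferroni rule is misplaced too.** A 2 x 2 design has simple-effect follow-ups: groups at each of two times and times within each of two groups, up to four comparisons. Bonferroni has a proper use there.
- **That incomplete cases will be dropped.** Multiple imputation is stated, although under the neuroimaging analysis heading, so its reach is arguable. The Quality Control and Informed Consent sections also say that data are collected whether or not participants complete, and are kept after withdrawal.
- **That N-Back load is wrongly omitted.** The test has three loads ("Each memory load level includes 3 blocks"), but whether they are analysed separately or as a factor is detail that an analysis plan may settle. Nothing says they are pooled.

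It is also fair to say that the redundant Greenhouse-Geisser sentence is harmless in itself, since epsilon = 1 changes no result. Its value is as a sign that the stated design is not settled.

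**Conclusion.** The point holds for the neuropsychological indicators, ANT and N-Back. Three visits are scheduled and two are modelled. The omitted one has a stated aim, so that aim has no stated estimate for these outcomes. The Greenhouse-Geisser rule cannot operate in the model as written.

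This rests on reading pretest and posttest as baseline and postintervention, and on counting MoCA among the neuropsychological indicators. The sphericity result needs no assumption. The outcomes affected are secondary and the trial is a pilot, so this is a correction that should be made before analysis, not a threat to the design. It matters because the pilot is meant to inform later trials, and a week-18 group difference with its interval is useful to whoever designs them.

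**What to change.** Before analysis, extend the stated model to week 18. The preferred form is a linear mixed model with the baseline value as covariate, postintervention and week 18 as visits, and group, visit and group-by-visit as fixed effects. Name the postintervention group contrast as the main test and the week-18 group contrast as the persistence estimate, each with a 95% CI. State that the same model applies to MFI-20 and PSQI.

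A 2 x 3 ANOVA over baseline, postintervention and week 18 would also reconcile the passages. Keep the sphericity sentence only if a within-person factor with three or more levels is in the model; otherwise delete it.

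The cost is a few lines of analysis wording and a standard procedure in SPSS, the software the article already names. The week-18 measurements are already scheduled, so no new data are needed and the sample size does not change.

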### Randomization and Allocation Concealment

Patients diagnosed with CFS who have signed the informed consent forms will be randomly assigned to either the Tai Chi group or the health education group at a 1:1 ratio. The random number table will be generated by researchers who are not involved in recruitment or intervention, using a computer. Each random number will be sealed in a pre-prepared opaque envelope with the patient’s sequence number. After providing written informed consent, participants will open an envelope labeled with their sequence number to learn which group they have been assigned to.

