In the experimental condition, participants are required to place their hands on the keyboard and focus their eyes on the fixation point in the center of the computer monitor. They must make a fast and accurate autonomous response based on the direction of the target stimulus. Specifically, if the central arrow of the target stimulus points left, participants are instructed to press the “F” key. If the central arrow points right, they should press the “J” key. The software automatically records the participant’s accuracy and reaction time. The task begins with 24 practice trials, followed by the formal experiment, which is divided into 3 blocks, each containing 96 trials. Participants are allowed to rest appropriately between blocks and can start the next block by pressing the space bar on the keyboard. The distribution of cue stimuli and target stimuli is balanced to ensure equal representation across trial types. The total duration of the task is approximately 30 minutes. The behavioral metrics include accuracy rate (higher is better), reaction time (faster is better), alerting score (no-cue reaction time [RT] to neutral-cue RT), orienting score (neutral-cue RT to spatial-cue RT), and conflict score (incongruent RT to congruent RT).

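### The 2 × 2 repeated measures ANOVA for the cognitive outcomes amounts to a change-score test: valid, but less precise than ANCOVA on the pretest that is already collected

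*Protocol article*

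**What the plan says.** The Statistical Analysis section assigns one model to a named set of outcomes, "For the neuropsychological test outcome indicators, ANT, and N-Back test behavioral metrics", with two groups and two times: "time: pretest, posttest) repeated measures ANOVA will be used". It adds: "All statistical inferences will be 2-tailed, with the level of significance set at α=.05". It does not state which term of the model answers the treatment question, and the article nowhere mentions ANCOVA or the pretest as a covariate.

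The pretest exists for these outcomes. Under Outcome Measure Assessment, MoCA, ANT and N-Back "will be assessed at baseline (week 1), at the end of the intervention (week 13), and at follow-up (week 18"). Under Demographic and Clinical Characteristics: "Baseline assessments will be completed before randomization". Participants are then "randomly assigned to either the Tai Chi group or the health education group at a 1:1 ratio".

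The ANT section defines the alerting, orienting and conflict scores as comparisons of two reaction-time conditions, for example the "conflict score (incongruent RT to congruent RT").

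**The concern.** With only two time points, the group-by-time interaction carries the same information as a t test on change scores. Each patient's pretest is subtracted in full, whatever its actual relation to the posttest. When the two are only moderately correlated, full subtraction adds pretest error to the comparison. ANCOVA estimates the slope from the data and so avoids this.

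What is at stake is precision. Cognition is in the trial's title and objective, there are at most 30 patients per arm, and the pilot is meant to supply estimates for a larger trial. Wider intervals than the data require weaken that purpose.

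**Working it through.** **The plan's own figure.** The sample size was set on MFI-20. The pooled SD is √((2.11² + 3.29²)/2) = 2.764, so d = (7.13 − 4.80)/2.764 = 0.843. A two-sided two-sample t test at .05 then needs 24 per group (power 0.816; 23 gives 0.798), and 24/(1 − 0.20) = 30. The stated figures reproduce. They supply the arm sizes used below, 24 completers out of 30, but claim no power for the cognitive outcomes.

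**Interaction and change score.** On simulated data with 30 per arm, the interaction F of the 2 × 2 model equalled the squared t for change scores to about 1e-14, as the algebra requires.

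**Variances.** Take equal SDs at both times and pre-post correlation rho. In units of SD², the per-arm variances are:
- posttest only: 1
- change score: 2(1 − rho)
- ANCOVA: 1 − rho²

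The ratio of change score to ANCOVA is 2(1 − rho)/(1 − rho²) = 2/(1 + rho), which exceeds 1 for every rho below 1. Estimating the slope costs ANCOVA a small-sample factor. With a normal covariate and N = 48 this is (N − 3)/(N − 4) = 45/44, so the ratio becomes 2/(1 + rho) × 44/45.

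**Assumptions.** The protocol gives neither rho nor an expected cognitive effect. I assume rho from 0.2 to 0.8, a true posttest difference of 0.6 SD, 24 completers per arm and two-sided .05. Power for the interaction is from the noncentral t with d = 0.6/√(2(1 − rho)). For ANCOVA the first figure uses d = 0.6/√(1 − rho²), and the second is simulated with the slope estimated.

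| rho | 2(1 − rho) | 1 − rho² | Ratio, large sample | Ratio × 44/45 | Power, interaction | Power, ANCOVA (formula / simulated) |
|---|---|---|---|---|---|---|
| 0.2 | 1.60 | 0.96 | 1.67 | 1.63 | 36% | 55% / 54% |
| 0.3 | 1.40 | 0.91 | 1.54 | 1.50 | 41% | 57% / 56% |
| 0.5 | 1.00 | 0.75 | 1.33 | 1.30 | 53% | 65% / 64% |
| 0.7 | 0.60 | 0.51 | 1.18 | 1.15 | 75% | 81% / 80% |
| 0.8 | 0.40 | 0.36 | 1.11 | 1.09 | 90% | 92% / 92% |

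Simulated variance ratios agree within a few hundredths: about 1.60 to 1.64 at rho 0.2, and 1.08 to 1.10 at rho 0.8. With 24 per arm the small-sample cost cancels the gain only above rho = 2 × 44/45 − 1 = 0.956.

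A t test that ignores the pretest has 53% power here. Below rho 0.5 the change-score test therefore does worse than making no use of baseline. If all 30 per arm are retained, the formula gives 49% against 67% at rho 0.3 and 63% against 75% at rho 0.5.

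**Other terms of the model.** The group main effect averages pretest and posttest, so it dilutes any effect. At a difference of 0.5 SD with 30 per arm, its simulated power was about 17% to 21%, against 37% to 68% for the interaction over rho 0.3 to 0.7.

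**The case against.** The strongest reply is that nothing here is an error. Baselines precede randomization, so the change-score test is unbiased and keeps its type I error. It is a conventional model, used for secondary outcomes in a pilot whose Discussion already warns of limited power. All of that stands, and it limits the point to one of efficiency.

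Four stronger readings are tempting, and the article does not support them.

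- *The pretest is noisy for every cognitive outcome.* Low rho is plausible for the three ANT difference scores, because each carries the error of two condition means. Overall ANT reaction time and accuracy rest on 3 blocks of 96 trials, and N-Back on 90 stimuli per load. No reliability is given for any of them, and if rho is 0.7 to 0.8 the gain is only about 2 to 6 power points.
- *The plan declares the interaction as its treatment test.* It names the model and no term. The interaction is the natural reading, and the group main effect would be weaker still.
- *The plan misses its stated power for cognition.* It states none. The 80% refers to MFI-20.
- *The test can be picked after the data are seen*, because the same section says: "For quantitative data with a nonnormal distribution and outcome indicators, the rank-sum test will be used". The sentence is awkwardly worded. However, the following paragraph names ANT and N-Back specifically and attaches no normality condition, so it can be read as governing them. The Blinding section also keeps statisticians blinded until the analysis is complete. I do not rest anything on this.

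**Conclusion.** The concern holds as a loss of precision. Read as a test of the interaction, the planned analysis has about 1.6 times the variance of ANCOVA at rho 0.2, falling to about 1.1 times at rho 0.8. At 0.6 SD with 24 per arm, the cost is roughly 18 power points at rho 0.2, 11 to 12 at rho 0.5 and 2 at rho 0.8. The direction does not depend on the assumed values, given equal SDs and rho below about 0.95. The size does: rho and the 0.6 SD are my assumptions. A material loss is most likely for the ANT alerting, orienting and conflict scores; for the other metrics it may be small. There is no bias and no inflation of false positives.

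**What to change.** For each cognitive score, replace the 2 × 2 ANOVA by ANCOVA of the posttest score on arm, with the pretest score of the same measure as covariate. Report the adjusted between-group difference with its 95% CI. This also settles which quantity is the treatment effect.

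The cost is a change of analysis wording and one degree of freedom per outcome. No new data or visits are needed, and the Results section says that statistical analysis has not yet been performed, so the change can still be made ahead of it. It is a free improvement rather than the repair of an invalid test.
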